## **Study algorithm**

Each team will participate in two simulation scenarios (i) term and (ii) preterm. With 3 teams, there will be total of 6 simulation experiments. Each team will undergo one scenario with a team leader and another scenario without a team leader. The sequence in which each team is allocated with/without team leader would be alternating with each team. For example, if team #1 starts with team leader for their preterm scenario, team #2 would participate same preterm scenario without team leader. This will ensure that both scenarios have an equal number of scenarios with and without a team leader.

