## **Simulation**

Prior to each simulation, participants will receive briefing about features of simulation dolls (i.e., to mimic the patient), how they need to assess the doll, and what information they need to obtain from the simulation instructors. Before each scenario each team will have approximately five minutes to prepare for the simulation. We will have two scenarios, one with management of an extreme preterm infant and another with the management of a term newborn with complications at delivery. Details of term and preterm resuscitation scenarios are provided in Appendix-1 and Appendix-2. Both these scenarios were used previously in our neonatal unit simulations. Both the simulation scenarios will need endotracheal intubation with the term baby scenario needing chest compression and umbilical vein administration of epinephrine. We will use the SimNewB (Laerdal Medical, Laerdal, Stavanger, Norway) low

HUFIN\_V5\_March 2022 IRAS: 314695 10

fidelity manikin for term and Premature infant Anne-low fidelity (Laerdal Medical, Laerdal, Stavanger, Norway) for the preterm scenarios, respectively. The two scenarios will be the same for all participants. We will run the two simulation scenarios with three different teams, giving a total of 6 scenarios. Each scenario will be running approximately for 10-15 minutes.

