## Statistics

This is an exploratory study consisting of XXX groups. To the authors knowledge, there has yet to be a comprehensive analysis of VA with eye-tracking in neonatal simulations examining impact of a team lead with a checklist. However, there has been a pilot study using eye-tracking in neonatal resuscitation which used a dataset of 6 participant video-based eye-tracking recordings of 5mins duration. Therefore, our anticipated dataset size of 24 participants, will provide greater insight to examine VA behaviour differences and detect impact of a team lead with a standardised checklist. Data will be analysed in SPSS (v23, IBM) and R studio (R. RStudio, Boston, MA, USA). To conform to the exploratory nature of the work, descriptive statistics such as means, and ranges will be used here based on the number of participants stratified across 4 teams. Independent t-tests will further explore any observable differences. Those data will be complimented with simple plots. Anonymised data will be made available on reasonable request.

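### Alternating three teams cannot give the equal with- and without-leader split in each scenario that the protocol says it ensures; the split is 2:1, and an unadjusted leader contrast carries one third of any preterm-term difference

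*Protocol*

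**What the plan says.** The Simulation and Study algorithm sections agree on the size of the experiment: "We will run the two simulation scenarios with three different teams, giving a total of 6 scenarios" and "With 3 teams, there will be total of 6 simulation experiments". Study algorithm then fixes the structure: "Each team will participate in two simulation scenarios (i) term and (ii) preterm", and "Each team will undergo one scenario with a team leader and another scenario without a team leader". The allocation rule is systematic: "The sequence in which each team is allocated with/without team leader would be alternating with each team". Its example gives team 1 a leader for preterm and team 2 the same scenario without one. The section concludes: "This will ensure that both scenarios have an equal number of scenarios with and without a team leader".

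The Simulation section says that both scenarios need intubation, "with the term baby scenario needing chest compression and umbilical vein administration of epinephrine". The Statistics section plans descriptive statistics and adds: "Independent t-tests will further explore any observable differences". It names no adjustment for scenario. It also refers to four teams and 24 participants, against three teams in the design sections and 18 participants under Sample size.

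**The concern.** The equality sentence is the only safeguard the protocol states against mixing up the leader's effect with the scenario's. If it fails, the with- and without-leader groups contain different proportions of preterm and term runs, and a plain comparison attributes part of the scenario difference to the leader.

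There is reason to expect some scenario difference. Chest compressions, medication administration and umbilical vessel catheterisation are three of the seven sub-domains of the team performance tool, and umbilical catheterisation is one of the listed areas of interest for eye-tracking. The tasks therefore bear on visual attention and team performance, and plausibly on workload. A reader who trusts the sentence would see no need to look at results by scenario.

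**Working it through.** **Inputs.** Three teams, two scenarios per team, one run with and one without a leader per team, alternation by team (Study algorithm). Control value 35% with SD 8 and target 55% (Sample size), so the target effect is 55 − 35 = 20 points. The preterm-term difference, D = preterm minus term, is not given anywhere and is treated as an assumption.

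**Run count.** 3 teams × 2 scenarios = 6 runs, as stated. Each scenario is run 6 / 2 = 3 times. The stated equal split would need 1.5 runs with and 1.5 without a leader per scenario, so it cannot be reproduced.

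**Alternation, following the protocol's example.**

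| Team | Preterm | Term |
|---|---|---|
| 1 | leader | no leader |
| 2 | no leader | leader |
| 3 | leader | no leader |
| With : without | 2 : 1 | 1 : 2 |

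Starting team 1 the other way mirrors the table.

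**Pooled contrast.** Let P and T be the scenario means without a leader and L the leader effect, assumed the same in both scenarios.
- Mean with leader = L + (2P + T)/3
- Mean without leader = (P + 2T)/3
- Difference = L + (P − T)/3 = L + D/3, or L − D/3 under the other start.

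**Within-team contrast.** The three leader-minus-no-leader differences are L + D, L − D and L + D. Their mean is (3L + D)/3 = L + D/3, so comparing the same people does not remove the term.

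**Other allocations of three teams.** Enumerating all eight gives coefficients of D of ±1/3 or ±1, never 0. With four teams alternation gives 2:2 in each scenario and a coefficient of 0.

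**Size for assumed values of D, with L = 20.**

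| Assumed D (points) | Bias D/3 | Crude contrast |
|---|---|---|
| 0 | 0 | 20.0 |
| 5 | 1.7 | 21.7 |
| 10 | 3.3 | 23.3 |
| 15 | 5.0 | 25.0 |
| 20 | 6.7 | 26.7 |

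**Cost of adjusting, three teams kept.** A least-squares fit with a scenario term returns L = 20 exactly for every D tried (5, 10, 20 and 30). It gives the same estimate as averaging, with equal weight, the mean difference of teams 1 and 3 and the difference of team 2.
- Variance: 0.75σ² adjusted against (1/3 + 1/3)σ² = 0.667σ² crude; ratio 1.125.
- Run level: residual df falls from 6 − 2 = 4 to 6 − 3 = 3, so the critical t goes from 2.776 to 3.182. Interval width ratio = √1.125 × 3.182/2.776 = 1.061 × 1.146 = 1.22.
- Within-team differences: df falls from 2 to 1 and the critical t goes from 4.30 to 12.71. Ratio = 1.061 × 12.71/4.30 = 3.1.

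Both ratios hold the residual SD fixed.

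**When adjustment pays at σ = 8.** Added variance = (0.75 − 0.667) × 64 = 5.3. Squared bias is D²/9: 2.8 at D = 5 and 25 at D = 15. They are equal at D = √(9 × 5.33) ≈ 6.9 points.

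**The case against.** The strongest reply has four parts.

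*The root error is the team count.* Statistics speaks of four teams, and with four the sentence would be true. This stands in part: the conflict must be resolved. But two design sections fix three teams and six runs, and Sample size also gives six scenarios, so the sentence fails on the design that is described. Reading it as overall totals (three runs with, three without) does not help, because it speaks of both scenarios; the overall equality already follows from each team doing one of each.

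*The size of the bias is unknown.* This stands. A reader might infer that the study will be biased by, say, 5 points, a quarter of the target. The protocol supports only the coefficient of one third: it shows that the tasks differ, not by how much the outcomes do. With the quoted SD of 8, the standard error of the crude difference is 8 × √(2/3) = 6.5 points, so a bias of 1.7 to 6.7 is about one standard error or less. At the low end, adjustment would increase mean squared error.

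*The analysis may yet handle scenario.* This also stands. The study is exploratory, the t-tests are not said to pool the scenarios, and a statistical analysis plan not shown might adjust. It does not make the design sentence true.

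*Learning.* A reader might infer that learning also biases the contrast, since the example has team 1 begin with preterm and each run is followed by a debrief. That follows only if all teams take the scenarios in the same order, which the protocol does not fix. If they did, order would coincide with scenario and a scenario term would absorb both.

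**Conclusion.** The claimed balance does not exist with three teams. The split is 2:1 and 1:2, and an unadjusted leader contrast equals the leader effect plus or minus one third of the preterm-term difference. This is certain from the protocol's own design and assumes only that the leader effect is the same in both scenarios.

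What is not established is a material bias. That depends on a scenario difference the protocol does not give and on an analysis it specifies only loosely. For an exploratory pilot this is a point that should be fixed, because a stated design property is false and easily corrected; it is not a reason to regard the main comparison as invalid.

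**What to change.** 1. Correct the equality sentence in Study algorithm and state the 2:1 split as a limitation. This is a change of wording only.
2. Reconcile the number of teams across Simulation, Study algorithm, Sample size and Statistics.
3. Show results by scenario. This needs no further data.
4. If three teams are kept, report a scenario-adjusted leader estimate beside the crude one, not in place of it. The price is the wider interval derived above, which is severe if the analysis uses averaged within-team differences on one degree of freedom.

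Using four teams would make the sentence true. If only three are planned, however, that means one more team (four more staff, by the stated team composition) and two more runs. It should be costed as a design change and not presented as a wording change.

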## **Briefing**

All scenarios will be preceded by locally developed standardised briefing including checklist of role allocation, equipment checking, and escalation plan. Most neonatal units will have this kind of checklist with some modifications to suit local set up. All the airway operators will be briefed about using eye-tracking wearable and undergo pre-simulation test for familiarity. Briefing will be done by the team leader, and we will use a local unit briefing checklist (Appendix-3).

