#### Secondary aims:

To examine impact of a team briefing prior to resuscitation on:

- 1) Team performance using the validated modified neonatal resuscitation performance evaluation (NRPE) tool, when (i) the operator is managing both airway and acting as team leader, compared to (ii) having a dedicated team leader with checklist.
- 2) Compare the workload with or without a team leader and standardised checklist. We will use National Aeronautics and Space Administration task load index (NASA-TLX) for assessing the workload.

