## **Materials and methods**

### **Study**

The clinical research question according to the patient, intervention, comparison, outcome, and time (PICOT) process is as follows:

- P: Neonatal resuscitation simulation scenarios, (i) preterm and (ii) term.
- I: Having dedicated airway operator and dedicated “resuscitation leader” (with and without a pre-briefing).
- C: Operator is managing both airway and acting as “resuscitation leader” (with and without a pre-briefing).
- O: Visual attention evaluated by eye-tracking, team performance and workload.
- T: Observational study in a simulation-based model.

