## Discussion

Here we provide a protocol for eye-tracking in neonatal resuscitation, with a focus on examining the impact of a team lead with a standardised checklist. At present there is no gold standard or proposed method for incorporating a team lead and/or checklist into neonatal resuscitation. This protocol will allow consideration of the combined and interactive impact of a team lead with a checklist for the field, considering the attentional demands using wearable eye-tracking video data to collect objective data to examine behaviour through visual attention.

This assessment paradigm distinguishes therefore itself from other work in the field. To the authors knowledge, no research has examined impact of a team lead with a checklist through use of a wearable eye-tracker, while also considering the scenarios of term and preterm in neonatal resuscitation. Furthermore, there hasn't been attempts explore team performance and workload. Therefore, the development and synthesis of this protocol will provide an important step in quantitatively assessing behaviour for appropriate clinical practice in neonatal resuscitation.

This protocol does carry some limitations. Firstly, there are several equivalent technologies that could be used for objective eye-tracking. However, given the lack of protocols in neonatal resuscitation, we feel the proposed manuscript provides a pragmatic starting point to work on and develop in future research.

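### The protocol promises the effect of a team briefing and its interaction with a dedicated leader, but every run is briefed, so neither can be estimated

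*Protocol*

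**What the plan says.** **What is promised.** The lead-in to the Secondary aims is "To examine impact of a team briefing prior to resuscitation on" team performance and workload. The second of those aims is to "Compare the workload with or without a team leader and standardised checklist". The PICOT, under Materials and methods (Study), describes both the intervention and the comparator as "with and without a pre-briefing". The Discussion states: "This protocol will allow consideration of the combined and interactive impact of a team lead with a checklist". Outcomes (Primary and secondary) and Statistics also describe the question as the impact of a team lead together with a checklist. The closing paragraph of the section on eye-tracking glasses in medicine says the study may inform the impact of using a checklist.

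**What is done.** The Study algorithm states: "Each team will undergo one scenario with a team leader and another scenario without a team leader", and "With 3 teams, there will be total of 6 simulation experiments". Leader yes/no is the only condition assigned within teams, apart from the term or preterm scenario. The Briefing section states: "All scenarios will be preceded by locally developed standardised briefing including checklist of role allocation, equipment checking, and escalation plan". On delivery, it says: "Briefing will be done by the team leader, and we will use a local unit briefing checklist". No section assigns any run to be without the briefing or the checklist.

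**The concern.** An effect can be estimated only if the factor takes at least two levels in the data. The aims, PICOT and Discussion treat the briefing as a factor that varies, while the conduct sections hold it constant. If both stand, a stated secondary question has no comparator. The practical risk is misattribution: a difference between leader conditions, seen with everyone briefed, could be reported as evidence for the checklist. The introductory text ties the checklist result to use in resource-limited settings, so such a claim would reach the purpose the study gives for itself.

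**Working it through.** **Inputs.** 3 teams with 2 runs each, giving 3 × 2 = 6 runs (Study algorithm). Each team has one run with and one without a leader, giving 3 and 3 (Study algorithm). Briefing with checklist before all scenarios, giving 6 of 6 (Briefing).

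**The plan's own sample size.** The Sample size section uses 35% of time on the infant (SD 8), a target of 55%, 80% power and alpha 0.05. Sidedness is not stated; I assume two-sided and the normal approximation.

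n per group = 2 × (1.960 + 0.842)² × 8² / 20² = 2 × 7.85 × 0.16 = 2.51, rounded up to 3.

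This reproduces the stated 3 per group and 6 scenarios. The comparison it sizes is leader against no leader. No run is budgeted for a briefing contrast. Whether the normal approximation is adequate at this size is a separate matter.

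**Cells of the two-by-two that the PICOT implies.**

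| | Briefed | Not briefed |
|---|---|---|
| Dedicated leader | 3 runs | 0 runs |
| No dedicated leader | 3 runs | 0 runs |

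**What these cells identify.** Let L = 1 with a dedicated leader and B = 1 with a briefing, and write the expected outcome as

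E(Y) = b0 + b1·L + b2·B + b3·L·B.

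With B = 1 throughout:

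- leader runs have mean b0 + b1 + b2 + b3;
- comparator runs have mean b0 + b2;
- the difference is b1 + b3, the leader effect given that the team is briefed.

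Two means cannot yield four parameters. In the 6 × 4 design matrix the briefing column equals the intercept column and the interaction column equals the leader column, so the rank is 2. The briefing effect without a leader (b2), the interaction (b3) and the combined effect against neither (b1 + b2 + b3) each need at least one empty cell.

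**Does another reading rescue it?** Suppose the briefing took place only in runs with a dedicated leader, so B = L. The leader runs then have mean b0 + b1 + b2 + b3 and the comparator runs b0. The rank is again 2. The difference is now the leader-plus-briefing bundle, and its parts still cannot be separated. Neither reading yields a briefing effect or an interaction.

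**Could the PICOT mean a different briefing?** The Simulation section describes an orientation on the manikins, but that too is given before each simulation, so it offers no contrast either.

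**The case against.** The best defence is that little of substance is lost. The study is a pilot, described as observational and exploratory. The primary aim and the sample size concern the leader contrast only. Both numbered secondary aims are, in substance, comparisons of team performance and workload with and without a dedicated leader, which the design delivers. On this view the fault is a loosely worded lead-in, a PICOT parenthesis and a sentence in the Discussion.

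Much of that stands, and it limits the point to secondary claims. It does not remove it. Exploratory status excuses low precision, not a missing comparator, and a statistical analysis plan cannot supply data for an empty cell. The wording also recurs in Outcomes and Statistics.

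A reader might go further and infer that leader and checklist are completely confounded, because the first secondary aim attaches the checklist to the dedicated-leader condition and the Briefing section has the team leader give the briefing. The documents do not support this. The Briefing section covers all scenarios and does not say that the leader who briefs must be a dedicated one. In the Primary aims and the PICOT the airway operator acts as leader in the comparator, so whoever leads may be the one who briefs. What the text shows is only that the briefer in runs without a dedicated leader is not specified.

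Nor does it follow that the primary contrast is compromised. If the briefing is constant, as written, that contrast is unaffected.

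**Conclusion.** The contradiction is real and lies within the protocol. With 0 of 6 runs unbriefed, 2 of the 4 implied cells are empty, and neither the briefing effect nor its interaction with the leader can be estimated. More teams under the same scheme would not change this. The leader effect with every run briefed remains estimable. The conclusion rests on taking the Briefing section at its word that all scenarios are briefed; the alternative reading, a briefing only with a dedicated leader, also fails to separate the two. It does not depend on any sample-size assumption. The text does not establish that leader and checklist are confounded or that the primary comparison is damaged. The secondary claims need correcting because they determine what the study may conclude.

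**What to change.** **Wording.**

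- Restate the Secondary aims as the effect of a dedicated leader on the modified NRPE and on NASA-TLX, with the same checklist briefing in all runs.
- Delete "with and without a pre-briefing" from both PICOT lines and remove the combined and interactive claim from the Discussion.
- Wherever the team lead is coupled to a checklist (Secondary aims, Outcomes, Statistics, Discussion), refer to the team lead alone.
- Amend the checklist-impact statement that closes the section on eye-tracking glasses, so that no checklist effect is claimed anywhere.

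**Conduct.** State who gives the briefing in runs without a dedicated leader and confirm that the checklist content is the same in both conditions. If the briefer differs by condition, report that as part of the leader contrast. Having a neutral person brief every run is possible but not required: it would take away a task the protocol gives to the team leader, and so change the intervention and not merely the wording.

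**Cost.** Text edits and one operational clarification, with no added runs. The study gives up a secondary claim that it cannot support.

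**Alternative.** If the sponsor wants to keep the briefing question, unbriefed runs must be added and sized. Merely filling the two empty cells to the present 3 runs each adds 2 × 3 = 6 runs, for 12 in total. That figure is a cell count, not a power calculation, and the change is a much larger one.

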## **Debriefing**

After completing the scenario, team will be provided debrief immediately after completing the simulation. All the debrief would be provided by the same investigator (NLS instructor) who is not involved in the outcome assessment. We would use local unit debrief checklist developed based on the method of debrief as described by Skare et al. This method has three phases: descriptive, analytical, and reflective (Appendix-4). During debrief, we will collect feedback with regards: 1) How did the simulation went? 2) What were the good things? 3) Things to improve 4) How they felt during the simulation?

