
Figure S1. SPIRIT Figure

|                             | STUDY PERIOD |            |                                 |                            |       |           |       |
|-----------------------------|--------------|------------|---------------------------------|----------------------------|-------|-----------|-------|
|                             | Enrolment    | Allocation | Post-allocation                 |                            |       | Close-out |       |
| TIMEPOINT**                 | $-t_1$       | 0          | $t_1$
(with
team
lead) | $t_2$ (no
team
lead) | $t_3$ | $t_4$     | $t_5$ |
| ENROLMENT:           |              |            |                                 |                            |       |           |       |
| Eligibility screen          | X            |            |                                 |                            |       |           |       |
| Informed consent            | X            |            |                                 |                            |       |           |       |
|                             |              |            |                                 |                            |       |           |       |
| Allocation                  |              | X          |                                 |                            |       |           |       |
| INTERVENTIONS:
NA |              |            |                                 |                            |       |           |       |
| ASSESSMENTS:         |              |            |                                 |                            |       |           |       |
| Participant details         |              | X          |                                 |                            |       |           |       |
| Visual attention            |              |            | X                               | X                          |       |           |       |
| Team performance            |              |            | X                               | X                          |       |           |       |

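### The debrief appears to fall between the two runs being compared, and with three teams the alternating order can only split 2:1, so part of any second-run gain stays in the leader effect

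*Protocol*

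**What the plan says.** The Study algorithm section of the protocol sets up a within-team comparison: "Each team will participate in two simulation scenarios (i) term and (ii) preterm", and "Each team will undergo one scenario with a team leader and another scenario without a team leader". Order is set by rule: "The sequence in which each team is allocated with/without team leader would be alternating with each team". The worked example is that "if team #1 starts with team leader for their preterm scenario, team #2 would participate same preterm scenario without team leader", and the section concludes: "This will ensure that both scenarios have an equal number of scenarios with and without a team leader". The Simulation and Study algorithm sections both give three teams and six runs. The Statistics section refers to four teams.

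On feedback, the Debriefing section states: "After completing the scenario, team will be provided debrief immediately after completing the simulation". The debrief has three structured phases, is led by an NLS instructor who does not assess outcomes, and asks: "1) How did the simulation went? 2) What were the good things? 3) Things to improve 4) How they felt during the simulation".

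Figure S1 (the SPIRIT figure) labels t1 as the run with a team lead and t2 as the run without one. It shows no second sequence.

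**The concern.** A structured debrief on what to improve is a form of training. Placed between a team's two runs, it can change the second run, whichever condition that run carries. Visual attention, team performance and workload are all measured in both runs, and Table S2 plans a same-person comparison of visual attention, so each outcome is exposed.

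Balanced order would cancel such a gain on average. Three teams cannot be balanced, and the protocol gives two accounts of the order. The contrast reported as the effect of a dedicated leader could therefore contain part of a learning effect. Depending on which order is in the majority, that part could hide or exaggerate a benefit.

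**Working it through.** **When the debrief happens.** The protocol uses scenario and simulation for single runs: the Simulation section counts six scenarios over three teams, and the Workload section has NASA-TLX completed after each simulation. With two runs per team, a debrief immediately after the scenario falls after run 1 and before run 2. No section defers it to the end of the session. The interval between a team's runs is not stated.

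**The plan's own figure.** The Sample size section gives 35% (SD 8) against 55%, 80% power and alpha 0.05. By the two-sided normal approximation, n per group = 2 × [8 × (1.960 + 0.842) / 20]² = 2.51, rounded up to 3. This reproduces the stated 3 per group. The standard error of the difference is 8 × √(2/3) = 6.5 points and power is 86.5%. (With the t distribution, power at 3 per group is 63.6%.) The order problem does not come from an error in this figure.

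**Bias from order.** Let T be the true leader effect and L the gain from first to second run, from debrief and practice together. A leader run contains L when it comes second, and a no-leader run contains L when the leader run came first. If p is the share of teams starting with the leader,

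expected leader minus no-leader = T + (1 − p)L − pL = T + (1 − 2p)L.

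- Three teams, two leader-first (p = 2/3): T − L/3.
- Three teams, one leader-first (p = 1/3): T + L/3.
- Four teams, 2:2 (p = 1/2): T.
- All leader-first, as Figure S1 shows (p = 1): T − L.

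**Size.** The documents do not give L. Values of 2 to 15 percentage points of time on the infant are assumed here for illustration. With T = 20, the planned difference, the expected estimates are:

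| L (assumed) | Two of three leader-first | One of three leader-first | Four teams, 2:2 | All leader-first |
|---|---|---|---|---|
| 2 | 19.3 | 20.7 | 20 | 18 |
| 5 | 18.3 | 21.7 | 20 | 15 |
| 10 | 16.7 | 23.3 | 20 | 10 |
| 15 | 15.0 | 25.0 | 20 | 5 |

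Under alternation with three teams the bias is 2/3 = 0.7 to 15/3 = 5 points in either direction. On the normal approximation with 3 per group, power falls from 86.5% to 84.1%, 80.1% and 72.3% for L = 2, 5 and 10 when two teams start with the leader. If all started with the leader it would be 78.7%, 63.2% and 33.4%.

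**The equal-numbers statement.** With three teams each scenario is run three times. An odd number of runs cannot be divided equally between with and without a leader, so the split is 2:1 within each scenario. If every team meets the scenarios in the same order, a difference in difficulty between term and preterm adds to the run-order effect with the same weight.

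**The case against.** A reader might infer from Figure S1 that every team has its leader run first, so that order and leader are fully confounded. The documents do not support that as the plan. The figure is a partly unedited template: it keeps the instruction to list timepoints, and its columns t3 to t5 are empty. It may only mark which assessments occur under each condition. The Study algorithm gives an explicit alternation rule with an example, and this is the more likely plan. What stands is that the two disagree and must be reconciled.

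A reader might also infer that the order effect can never cancel, or that the debrief is known to shift attention. Neither follows. The four teams under Statistics could be split 2:2. Nothing in the documents shows that a verbal debrief changes time on the infant, the two runs are different scenarios, and carry-over may be small. Under alternation the illustrative bias stays below the planned standard error of 6.5 points. The study also describes itself as a pilot and exploratory.

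These points limit the size but do not remove the problem. Bias adds to sampling error and does not average out with it. An analysis plan not shown here may include a run-order term, and its absence from the protocol is not criticised. With three teams, however, one order rests on a single team, so such a term would be poorly estimated, and prevention by design is safer.

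**Conclusion.** The point holds in a limited form. On the natural reading, feedback is given between the two runs being compared. With three teams, one third of any second-run gain remains in the leader contrast: against the leader if two teams start with one, in favour if only one does. For an assumed gain of 2 to 15 points this is about 0.7 to 5 points against a target of 20. The equal numbers promised in the Study algorithm are impossible with three teams. A bias equal to the whole gain, against the leader, arises only if Figure S1 is followed in place of the text.

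The 2:1 split and the conflict over order follow from the documents. The timing of the debrief is a reading of the text, though the natural one. The size rests entirely on the assumed L.

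**What to change.** - Hold the debrief until the team has finished both scenarios. NASA-TLX is already planned after each run; state that it is completed before any feedback. The planned recordings can support a joint debrief.
- Relabel the Figure S1 columns as run 1 and run 2, with the condition set by the alternating sequence.
- Reconcile the number of teams (three or four). An even number allows balanced order. If it stays at three, drop the equal-numbers statement and acknowledge that residual practice effects remain at 2:1 weight.

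Moving the debrief removes only its own part of L. Practice and familiarity remain, so the number of teams still matters.

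The first two changes are a matter of scheduling and a figure correction. The downside is that feedback on the first run comes later, and comments on how each run went and felt may blend. Asking the debrief questions separately for each run would limit this. A fourth team, if chosen, would add two runs.
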